## Abstract

**Introduction:** Telemedicine can address limited access to medical specialists in rural hospitals. Stroke provides an important case study because: it is a major cause of disease burden; effective treatments to reduce disability (e.g., thrombolysis) can be provided within the initial hours of stroke onset; careful selection of patients is needed by skilled doctors to minimize adverse events from thrombolysis; and there are major treatment gaps (only about half of regional hospitals in Australia provide thrombolysis for stroke). Few economic analyses have been undertaken on telestroke and the majority have been simulation models. The aim of this protocol and statistical analysis plan is to outline the methods for the cost-effectiveness evaluation of a large, multicentre acute stroke telemedicine program being conducted in Victoria, Australia.

**Methods:** Using a historical- and prospective-controlled design, we will compare patient-level data obtained in the 12 months prior to the Victorian Stroke Telemedicine (VST) program implementation and during the first 12 months of VST to determine the incremental difference in costs and patient outcomes at 3 and 12 months. Secondary aims include assessing the cost per additional patient receiving intravenous thrombolysis and the cost per additional patient receiving intravenous thrombolysis within 60 min. Tertiary aims include assessing the potential longer-term cost-effectiveness in the second year of the program at the hospitals to determine whether any program benefits are sustained once site coordinators are no longer employed; and modeling the potential net life-time costs and benefits from a societal perspective. Multivariable uncertainty and one-way sensitivity analyses will be performed to assess the robustness of results.

**Results:** Sixteen hospitals participated. Patient-level data collection including 12-month outcomes for the cohorts obtained in the first and second year of the program for each hospital was completed in January 2020.

**Conclusion:** The results from this real-world study with patient-level data will provide high quality evidence of the costs, health benefits and policy implications of telestroke programs, including the potential for application in other locations within Australia or other countries with similar health system delivery and financing.

## Introduction

Worldwide, stroke is a major cause of death and disability and represents a growing burden of disease (1). There are effective treatments to reduce the impact of this disease (2). Unfortunately, many people with stroke do not receive effective treatments for various reasons including lack of symptom recognition (only 35% arrive at hospital within 4.5 h of stroke onset) (3), limited specialist services and poor knowledge translation of evidence. Within Australia, it is estimated that over 50,000 strokes occur each year (4) and only about 10% of patients with ischaemic stroke receive intravenous thrombolysis (3).

Telemedicine for stroke (i.e., telestroke) is a model of care that can facilitate timely access to medical specialists in hospitals with limited resources for stroke care (5, 6). The establishment of telestroke networks in various parts of the world has enabled the delivery of enhanced stroke care (7) and is one of the fastest growing areas of telehealth (8). This is because of the availability of effective treatment for stroke and pressures to improve quality of care for patients, as well as the high cost of air and ground ambulance transfer (8). There are various models of care that can be developed and establishing if these are cost-effective when compared with the standard care alternatives is important for informing decisions to invest in this type of service. Few economic evaluations of telestroke have been undertaken, mainly in Europe and North America, and cost-effectiveness has been mainly determined on the basis of simulation modeling of a societal and hospital perspective (8). Two previous economic evaluations conducted alongside historical controlled studies of stroke telemedicine in the United States that have used patient-level data have shown evidence that telestroke is cost-effective (9, 10).

Following a pilot period at one hospital in regional Australia, the Victorian Stroke Telemedicine (VST) Program commenced in 2013 and was incrementally expanded to 16 hospitals by 2016 (11, 12). The main features included access to a virtual roster of neurologists for assistance with clinical decision making and employment of a site coordinator in each hospital to integrate the VST protocol into routine emergency department (ED) workflows according to an implementation plan (typically completed within 6 months; with a further 12-months for data collection and support) (13). The establishment of the cost-effectiveness credentials of a state-wide program for Australia, such as VST, is needed since no other states or territories had implemented a coordinated approach to telestroke at the time this study began, and none have used patient-level data to determine cost-effectiveness. This protocol describes the methods for the economic evaluation of the VST program and the statistical analysis plan.

## Aims

The primary aim of the economic evaluation will be to determine the cost per quality adjusted life year (QALYs) gained at 12 months after stroke.

The secondary aims are to determine the cost per additional patient receiving intravenous thrombolysis and the cost per additional patient receiving intravenous thrombolysis within 60 min of arrival to hospital.

Tertiary aims include assessing the potential long-term cost-effectiveness of the VST Program using data collected during the sustainability period of the study when telestroke had become usual practice. The “sustainability period” was the second year of the telestroke program at the hospitals when the site coordinators were no longer funded to provide direct support for implementing the VST Program. We will also seek to assess the influence of adopting different perspectives (hospital vs. societal) to the measurement of costs and benefits including modeling the potential net life-time impacts.

## Methods

### Design

The economic evaluation, a sub-study of the clinical effectiveness project (12), will be a pragmatic, real-world, economic evaluation of the implementation and long-term impacts of the VST Program compared to standard care. The study design of the VST Program evaluation has been detailed previously (11–13). In brief, the study has a pre-post-test design with a combination of historical- and prospective-control patient-level data to provide evidence on standard care practice, made possible through the iterative addition of hospitals over 7 years. After training and a short pilot phase to refine the clinical protocol at each hospital, the VST Program was implemented and clinicians then have the ability to consult with a virtual network of stroke specialist doctors for diagnosis and treatment recommendations for patients presenting to their emergency departments (EDs) with suspected stroke (13). Prior to the VST Program commencing, only five of the 16 hospitals were routinely providing intravenous thrombolysis for patients with ischaemic stroke. The project is led by the Florey Institute of Neuroscience and Mental Health. As part of this sub-study, a cost-description analysis of each comparator (pre-post) pathway will be undertaken and then compared to determine the incremental cost-effectiveness and cost-utility of the VST Program (see below).

### Setting

EDs of 16 public hospitals located in regional Victoria, Australia. Data were collected from 2010 until 2020.

### Study Perspective

A societal perspective with a major focus on the health sector will be used for this evaluation.

### Patient Eligibility Criteria

Adult patients with suspected stroke who present to the ED of participating hospitals for assessment and treatment were included. These patients are identified using the following international classification of diseases (ICD10) codes assigned to patients in the ED: G45.9, I61.9, I62.1, I62.9, I63.9, I64, R41.0, R47.0, R47.1, S06.00, S06.01) and for admitted cases: I61, I62.9, I63, I64, I67.8, I67.9, G45.0, G45.1, G45.2, G45.3, G45.8, G45.9 (13).

A screening log is used to record information for each cohort and identify patients eligible for additional data collection. Patients with a confirmed stroke and arrived at the ED within 4.5 h of symptom onset, and those provided a VST consultation (irrespective of other clinical characteristics), have additional data collected using a purposefully designed, standardized medical record audit tool (see Data collection) (13).

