### Comparator “Standard Care” Control Cohort

All eligible patients who presented to the ED at a participating hospital during the 12-month period prior to implementation of VST.

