### Intervention Cohort

All patients who were eligible for inclusion in the first 12-month (implementation period) or presented to hospital in the subsequent 12-months (*second year: referred to as the sustainability period*) after the implementation of the VST Program.

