### Sample Size

The sample size for the economic evaluation is dependent on the number of patients presenting to the participating hospitals who meet the inclusion criteria. Data collected on over 1,000 patients will be available for the economic evaluation.

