Only patients with a confirmed stroke and who arrive at hospital within 4.5 h of symptom onset are eligible for a follow-up survey at 3-months and at 12-months to collect self-reported health outcome data (survival status, quality of life) and information on resource use (including readmissions to hospital, clinical visits, employment status and current residence). A modified Dillman protocol is used where the follow-up survey is posted to the patient's address 1 week prior to the assessment time point (14). If no response is received within 4 weeks, a second copy of the survey is sent to the patient's address and the address of a nominated alternate contact. If no response is received within 6 weeks of the initial contact attempt, program staff attempt contact with the patient and nominated alternate contact via telephone to complete the survey questionnaires. Patients are considered to be “lost to follow-up” if contact is unable to be made by 6 months post-stroke for the 3-month follow-up or by 15 months post-stroke for the 12-month follow-up survey.

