The strengths of our methods for this economic evaluation include the reliable patient-level data in the acute phase and detailed intervention costs. The final sample sizes for the clinical effectiveness study as of 31 December 2017 were 2,887 patients with suspected stroke in the control period and 3,178 patients with suspected stroke in the VST intervention period. There were no major differences in patient characteristics with suspected stroke between study periods, however more were provided an initial diagnosis of ischaemic stroke and had a documented time from symptom onset in the VST Program implementation cohort (13). The number of eligible patients for detailed audit was 423 for the control period and 601 in the intervention period (13). As of January 2019, 360 of the 764 eligible patients who could be sent an outcome survey at 3-months have provided survey responses following hospital admission (26 patients in the control period and 334 patients in the intervention period). Information from another 101 patients have been collected at 12 months after their hospital admission (88 in the control period and 13 in the intervention period).

Another strength of the economic evaluation will be the use of the EQ-5D to calculate the utility score for estimating QALYs gained. This will allow VST results to be compared with international studies which often use the EQ-5D instrument. In a recent review, there were very few well designed economic evaluations that could be used to usefully inform public health policy and investment decisions in general, highlighting an urgent need for greater application of economic evaluation to understand the cost-effectiveness of alternative implementation efforts (36). Our work will be an important contribution to the field of stroke and implementation research that is focused on improving uptake of evidence-based interventions in hospital settings.

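### A VST consultation alone admits intervention-period patients to the detailed audit, a route closed to controls, and nothing limits the acute-cost and thrombolysis comparisons to the shared criterion

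*Protocol article*

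**What the plan says.** Patient Eligibility Criteria (Protocol article) gives two routes into the detailed medical record audit. The first is open in either period: "Patients with a confirmed stroke and arrived at the ED within 4.5 h of symptom onset". The second depends on the intervention: "those provided a VST consultation (irrespective of other clinical characteristics), have additional data collected".

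The control cohort is "All eligible patients who presented to the ED at a participating hospital during the 12-month period prior to implementation of VST". The Intervention Cohort section takes eligible patients of the first programme year, and those presenting in the second, without excluding anyone who entered by consultation alone.

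According to Data Collection, the audit tool records treatment with thrombolysis, arrival and imaging times, and consultation details. Direct Healthcare Costs of Participants names the record audit as the source of acute-phase resource use. Sample Size states: "Data collected on over 1,000 patients will be available for the economic evaluation". The Discussion reports: "The number of eligible patients for detailed audit was 423 for the control period and 601 in the intervention period".

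Follow-up has a narrower rule, the same in both periods: "Only patients with a confirmed stroke and who arrive at hospital within 4.5 h of symptom onset are eligible for a follow-up survey".

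**The concern.** A patient whose stroke was not confirmed, or who arrived after 4.5 h, is audited if a VST consultation took place. The same kind of patient in the pre-VST year is not audited. If acute costs and thrombolysis are compared on the audited patients as they stand, the two periods are defined differently, and the difference depends on receiving the intervention.

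Two results are exposed:

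- **The secondary ratios.** Cost per additional thrombolysed patient, and per additional patient thrombolysed within 60 min, use acute data from this audit. Any thrombolysis proportion with audited patients as its denominator changes meaning between periods.
- **The acute-cost part of the primary ratio.** Acute costs may cover a wider intervention population than the QALYs and post-acute costs beside them, which come from surveyed patients only.

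The planned adjustment does not clearly repair this. The example cost model under Data Analysis uses age, sex, type and severity of stroke, length of stay and hospital. It does not include entry route, stroke-or-mimic status or time from onset to arrival. A consulted patient without stroke has no stroke type, and the planned stroke/TIA price mapping does not fit such a patient either.

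**Working it through.** **1. Is the audit set the economic data set?** Inputs are the audit-eligible counts in the Discussion: 423 control and 601 intervention.

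423 + 601 = 1,024. This agrees with the figure of over 1,000 under Sample Size. The match is an inference, because that figure is rounded and no analysis set is named.

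**2. Who can enter, by period?**

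| Patient | Control period | Intervention period |
|---|---|---|
| Confirmed stroke, arrival within 4.5 h | audited | audited |
| Not confirmed stroke, or later arrival, VST consultation | cannot occur | audited |
| Not confirmed stroke, or later arrival, no consultation | not audited | not audited |
| Eligible for 3- and 12-month surveys | first row only | first row only |

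The asymmetry is confined to the second row. It reaches audit-based acute data but not survey-based data.

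**3. Is there a trace of it in the counts?** Suspected strokes (Discussion): 2,887 control and 3,178 intervention. The calculation assumes these cover the same periods as the audit counts.

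- Control share: 423 / 2,887 = 14.65%
- Intervention share: 601 / 3,178 = 18.91%
- Difference: 4.26 percentage points; ratio 0.1891 / 0.1465 = 1.29
- Pooled share: 1,024 / 6,065 = 0.1688
- z = 0.0426 / √[0.1688 × 0.8312 × (1/2,887 + 1/3,178)] = 4.42
- Expected intervention count at the control share: 3,178 × 0.1465 = 466
- Excess: 601 − 466 = 135, or 22.5% of 601

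The share rose by more than chance would explain. The counts do not say why. The Discussion also reports that "more were provided an initial diagnosis of ischaemic stroke and had a documented time from symptom onset in the VST Program implementation cohort". Either change could raise the number of confirmed strokes within 4.5 h without a single consultation-only patient.

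**4. What would remain on the shared criterion?** The consultation-only fraction s of the 601 is not stated, so a range is assumed. The last column also assumes that none of these patients was thrombolysed. Under that assumption the thrombolysis proportion among all audited intervention patients equals (1 − s) times the proportion on the shared criterion.

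| s (assumed) | Intervention patients left | Total with 423 controls | Factor on thrombolysis proportion |
|---|---|---|---|
| 0% | 601 | 1,024 | 1.00 |
| 10% | 541 | 964 | 0.90 |
| 22.5% | 466 | 889 | 0.775 |
| 30% | 421 | 844 | 0.70 |

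The 22.5% row treats the whole excess from step 3 as consultation-only. It is one scenario, not an estimate. No corresponding figure for acute cost can be given, because the article does not say whether consultation-only patients cost more or less than the rest.

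**The case against.** The strongest reply is that the sentence on consultations is a data-collection rule. It says whose records are audited in detail, not who is analysed. No analysis set is declared, the cohorts are defined by eligibility and period, and a condensed article may leave the set to a fuller document. The wide rule also has a good purpose: neurologist time is costed per patient, so consultations for mimics and late arrivals must be recorded somewhere. All of this stands, and it rules out saying that the plan declares non-comparable analysis sets. It does not settle the point, because the audit is the named source of the acute data and nothing shown limits the comparison to the shared route.

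Two stronger readings are tempting and are not supported:

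- A reader might infer that the QALY comparison is built on different populations. The survey rule prevents this for observed EQ-5D data, since consultation-only patients receive no survey. They could contribute QALYs only through registry data, imputation or mRS-based utilities, and the article does not say that they would.
- A reader might take the excess of 135 as the number of consultation-only patients. The reported changes in diagnosis and onset recording make that attribution impossible.

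It can also be said that the Discussion already admits possible selection bias. It does so in general terms and does not mention this route.

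**Conclusion.** The point holds in a limited form. Entry to the detailed audit is asymmetric by construction, and as written the acute-cost and thrombolysis comparisons may be made on groups defined differently in the two periods. This reaches the acute-cost part of the primary ratio and both secondary ratios. Survey-based QALYs and post-acute costs already follow one criterion.

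The conclusion assumes that the 1,024 audited patients are the economic data set, which the counts support but the text does not state, and that no unseen document restricts the comparison. Neither size nor direction of bias can be computed from the article. The rise from 14.7% to 18.9% is consistent with the mechanism and does not measure it.

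**What to change.** 1. State that the between-period comparison of acute costs, thrombolysis and QALYs uses confirmed strokes arriving within 4.5 h of onset in both periods.
2. Charge the VST consultation costs of all other consulted patients to programme cost, so that this spending stays in the numerator. Report how many such patients there were.
3. As a sensitivity analysis, report additional thrombolysed patients per suspected-stroke presentation, with denominators 2,887 and 3,178. This is needed because onset was documented more often under VST, so the 4.5 h criterion may itself select more patients after implementation. Count treated patients by the same rule in both periods: a treated patient without confirmed stroke would reach the audit only in the intervention period.

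The cost is some wording and a filter on existing data, with no new collection. Somewhat fewer intervention patients remain in the acute-cost analysis. The third step removes dependence on recorded onset time for the thrombolysis results only. For costs and QALYs, that dependence remains and should be stated as a limitation.

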### Comparator “Standard Care” Control Cohort

All eligible patients who presented to the ED at a participating hospital during the 12-month period prior to implementation of VST.

### Intervention Cohort

All patients who were eligible for inclusion in the first 12-month (implementation period) or presented to hospital in the subsequent 12-months (*second year: referred to as the sustainability period*) after the implementation of the VST Program.

### Sample Size

The sample size for the economic evaluation is dependent on the number of patients presenting to the participating hospitals who meet the inclusion criteria. Data collected on over 1,000 patients will be available for the economic evaluation.

### Data Collection

Data are obtained via two methods to provide 12 months of pre-implementation data. An audit of patient records is conducted at each of the hospitals for the control group, but data collection was initially retrospective and limited to care provided and outcomes achieved in the hospital. Grant funding for this sub-study was obtained in 2015. Subsequently, where ethics approval was able to be obtained in advance of VST being implemented at a new hospital, we sought to obtain information from patients eligible for inclusion prospectively and conduct follow-up assessments at 3- and 12-months post stroke. Therefore, a sample of comparable long-term outcome data was obtained for part of the control group in this study.

Data collected using the standardized medical record audit tool includes patient characteristics on presentation to hospital (age, sex, stroke severity and pre-morbid function), management and treatment while in hospital (i.e., time of arrival and first brain imaging, treatment with intravenous thrombolysis), details of the telemedicine consultation (i.e., time and length of telemedicine consult) if applicable and outcomes at discharge from hospital (i.e., level of independence, adverse events while in hospital, discharge destination).

A waiver of consent is provided for the cohort whose data were collected retrospectively and an opt-out consent protocol is used for the cohort whose data are being collected prospectively in order to reduce the potential for selection bias. In the prospectively identified cohort, patients are provided with a consent form while in hospital or shortly after discharge from hospital.

Only patients with a confirmed stroke and who arrive at hospital within 4.5 h of symptom onset are eligible for a follow-up survey at 3-months and at 12-months to collect self-reported health outcome data (survival status, quality of life) and information on resource use (including readmissions to hospital, clinical visits, employment status and current residence). A modified Dillman protocol is used where the follow-up survey is posted to the patient's address 1 week prior to the assessment time point (14). If no response is received within 4 weeks, a second copy of the survey is sent to the patient's address and the address of a nominated alternate contact. If no response is received within 6 weeks of the initial contact attempt, program staff attempt contact with the patient and nominated alternate contact via telephone to complete the survey questionnaires. Patients are considered to be “lost to follow-up” if contact is unable to be made by 6 months post-stroke for the 3-month follow-up or by 15 months post-stroke for the 12-month follow-up survey.

